### 2.5. Procedures and Data Collection

The study will last eight weeks for each patient. On the first day (day 1), the investigator will ask the patient and his/her caregiver to answer the questionnaires.

For patients in the ButterfLife group, the investigator will deliver the ButterfLife device (Figure 2) at home and explain its use. ButterfLife is a medical device similar to a joypad, designed by the Unimore spinoff VST (Vital Signal in a Touch, VST Srl, Modena, Italy), which, through the use of three different sensors, a photoplethysmogram, electrocardiogram, and an infrared thermometer, simultaneously measures the five primary vital parameters defined by the World Health Organization in 90 s (heart rate, respiratory rate, blood oxygenation, blood pressure, and body temperature). The ButterfLife device is designed to make self-measurements and therefore requires no external intervention for measurements. To record these parameters, the patient has to place both hands on the device, and the data collected are immediately transmitted to a portal whose software (VST-FIVE) calculates the vital signs and allows visualization of the sharing with the doctor via a Wi-Fi network (https://my.vital.st/) (accessed on 22 December 2022). To guarantee a stable internet connection, a 4G LTE Wi-Fi Router (TP-Link, Hong Kong) will be provided at the patient’s home. In this way, it is possible to ensure the early detection of worsening and failure of the health state, enabling the timely activation of appropriate intervention in the home setting. The recorded data remains available for subsequent evaluation, long-term monitoring, and offline analysis. The patient is recommended to take the measurement once a day, preferably in the morning, and to repeat the measurement of parameters during the day if necessary. The investigator will leave a booklet containing simple written instructions with images explaining the use of ButterfLife. The doctor will check the data recorded by the patient every day (Supplementary Document 1) and the trend of the parameters over time by a graphical representation on the electronic medical record (Vitaever, Nethical Srl, Bologna, Italy) (https://www.vitaever.com/) (accessed on 20 December 2022). Daily telemonitoring will be conducted in addition to standard home care.

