### 2.6. Measures and Outcomes

The primary outcome of the study is the acceptability and the feasibility of the telemonitoring intervention measured as the percentage of eligible patients proposed for the study who agree to participate and the number of self-measurements/week per patient. Moreover, a questionnaire for evaluating the ButterfLife device (ease of use, difficulties encountered, and usefulness) was constructed based on several questionnaires already found in the literature [26] and will be administered to patients belonging to the ButterfLife group at the end of the telemonitoring period.

The secondary outcomes involving patients and caregivers are listed below.

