Moreover, a series of secondary outcomes will be evaluated on physicians, the ANT Foundation, and the National Health System:The acceptability and ease of use of the device will be assessed by a questionnaire directed to the physician.The number of scheduled, unscheduled, and on-call visits (doctor and nurse), as well as the number of phone calls and emergency phone calls received by the doctor and nurse, will be assessed.The number of admissions to the emergency room will be assessed.Hospitalization days will be assessed.

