### 2.10. Statistical Analysis

A statistical analysis will be conducted on the data after their anonymization. An investigator is in charge of anonymization and blinding to groups’ patient allocation. The anonymized and blinded data will be passed to the investigators in charge of data analysis. Anonymized data will be stored within the Research Department of the ANT Foundation in an ad hoc safe electronic database. The statistical analysis will be structured as follows:Descriptive analysis of the characteristics of the recruited subjects. The following parameters are shown as frequencies: age, sex, KPS, diagnosis, time since diagnosis, presence of metastases, symptoms, current therapies, and stage of the disease.Analysis of acceptability and feasibility: percentage of eligible patients proposed for the study who agree to participate, percentage of drop out from the study, number of measurements/week per patient, patient assessment of ease of use, difficulties encountered, and usefulness.The trend of secondary outcomes (QOL, psychological state, and caregiver care burden) over time (day 1, day 28 and day 56) will be analyzed using a general linear model for repeated measures.Comparison between the ButterfLife and Control groups: after analyzing the normality of the variables (Shapiro–Wilk test), the differences between the two groups for secondary outcomes (QOL, psychological state, caregiver care burden, caregiver satisfaction with the care received, number of scheduled visits, unscheduled visits, on-call visits, phone calls received by the doctor and nurse, number of visits to the emergency room, number of hospital admissions and hospitalization) will be analyzed with parametric (Student’s *t*-test) or non-parametric tests (Mann–Whitney test).

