We expect a significant level of engagement in terms of the number of self-measurements/week per patient, ease of use, difficulties experienced, and usefulness. In this feasibility study, engagement will be evaluated by some indicators as defined by Perski et al., 2017 (and echoed by Goodman et al., 2022), including the frequency and duration of measurements, depth of device use, and others [8,42].

Furthermore, this telemonitoring intervention may have a positive impact on the caregivers. Improving advanced cancer patients’ QOL and psychological symptomatology may relieve the care burden perceived by caregivers and enhance the family’s satisfaction with the care received from the healthcare team. Indeed, previous studies stated that the caregiver’s QOL is related to the patient’s [43], making clear that a possible strategy for enhancing the caregiver’s QOL is to improve the patient’s [44]. In addition, telemedicine may help family caregivers to maintain their personal habits and professional position and to limit financial consequences due to missed workdays required to accompany their loved ones to medical clinics or hospitals [45].

In the present setting, one of the motivations sustaining the advantages of telehealth implementation is the potential to lower home care costs, as well as to improve and expand access to healthcare services [45]. Telehealth could impact costs by relieving the healthcare team from some clinical activities, such as the monitoring of vital parameters at home and reducing travel and workload [45].

The evaluation of secondary outcomes, such as the intensity of doctor/nurse home visits, phone calls, hospital admissions, and hospitalization days, will return an indirect measure of the impact of this telemonitoring intervention in terms of costs and suitability of resources provided by home care services and the National Health System.

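### Only incoming calls are counted and service-use counts carry no observation time, so a change in call direction, or unequal loss between arms, can look like a change in service use

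*Protocol article*

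**What the plan says.** Section 2.6 of the protocol article lists scheduled, unscheduled and on-call visits, "the number of phone calls and emergency phone calls received by the doctor and nurse", emergency room admissions and hospital days ("Hospitalization days will be assessed"). Section 2.10 names much the same quantities for the group comparison, "number of scheduled visits, unscheduled visits, on-call visits, phone calls received by the doctor and nurse, number of visits to the emergency room" among them, and says that differences "will be analyzed with parametric (Student’s *t*-test) or non-parametric tests (Mann–Whitney test"). Neither section gives these counts a denominator or a rule for patients who die or leave before day 56. Dropout appears in section 2.10 only as a feasibility percentage. The self-measurement outcome, by contrast, is scaled to time: "number of self-measurements/week per patient".

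Section 2.5 describes how contact arises. In the ButterfLife arm, "The doctor will check the data recorded by the patient every day". In the control arm, a patient whose condition worsens can phone the physician or nurse. Section 3 says that visits, calls and hospital use "will return an indirect measure of the impact of this telemonitoring intervention in terms of costs".

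**The concern.** The first problem is what is measured. A contact that a control patient starts by phone is counted. The same contact, started by a physician who has seen an abnormal reading, is not. Outgoing calls prompted by daily review can arise in only one arm, so randomisation does not balance this out and dividing by time does not remove it.

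The second problem is comparability. Patients with advanced cancer may die or withdraw within eight weeks, and a patient seen for two weeks has less time to accumulate visits than one seen for eight. Someone with 6 visits in 2 weeks (3 per week) has a lower total than someone with 8 visits in 8 weeks (1 per week).

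At stake is the reading of cost and workload in section 3. Fewer recorded calls or visits could be taken as a saving when the amount of contact, or the rate of use, has not changed.

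**Working it through.** **Inputs.** From the article: 25 patients per arm (2.4, 2.9), eight weeks per patient (2.5), and the tests in 2.10. It gives no rate of contact, death or dropout, so there is no plan figure to reproduce here. Every rate below is an assumption.

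**1. Call direction.** Let a patient's total calls be *N* and the share that becomes outgoing be *s*. Calls received = *N*(1 − *s*), so the apparent saving is *s* while the true saving is 0. For *s* = 10%, 25% and 50%, received calls fall by 10%, 25% and 50%.

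Simulation: 20,000 trials, one call per week in total, patient rates varying by a gamma distribution with shape 2, 20% mortality in both arms. Mann–Whitney declares lower use in about 5%, 17% and 65% of trials. Run on calls per week, it still rejects in about 7%, 19% and 70% (either direction).

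**2. Observation time, constant weekly use.** Assume 1.5 contacts per week in both arms and early loss at a time uniform over 0–8 weeks. Mean observed time = 8(1 − *p*) + 4*p* = 8 − 4*p* weeks, where *p* is the share lost early.

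| Loss, Control v ButterfLife | Mean weeks | Mean totals | Difference | Mann–Whitney rejects |
|---|---|---|---|---|
| 30% v 30% | 6.8 v 6.8 | 10.2 v 10.2 | 0% | 4.8% |
| 20% v 35% | 7.2 v 6.6 | 10.8 v 9.9 | −8% | 6.1% |
| 10% v 40% | 7.6 v 6.4 | 11.4 v 9.6 | −16% | 9.7% |

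The last column is from 20,000 simulated trials with gamma–Poisson counts (dispersion 1). On counts per observed week it is 4.9% in all three rows. Swapping the arms reverses the sign.

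A second model (exponential death times, 2 contacts per week) agrees. Mean weeks are 7.17 at 20% mortality and 6.73 at 30%, so the ratio of totals is 6.73/7.17 = 0.94. At 50% v 20% it is 5.77/7.17 = 0.80.

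**3. Is imbalance plausible?** With the same true loss in both arms, two independent binomial counts of 25 differ by four or more patients in 21% of trials (loss 20%) or 28% (loss 30%). Four of 25 is 16 points, close to the 15-point gap in the second row. Over repeated trials the test keeps its level, but in any one trial the totals can shift this way and the reader could not see it.

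**4. If use rises before death.** Treat early loss as death and triple the rate in the last two weeks of life. The mean time spent at the higher rate, for those who die, is E[min(*t*, 2)] = 0.25 + 1.5 = 1.75 weeks, which adds 2 × 1.75 = 3.5 week-equivalents. For 20% v 35% loss:
- totals: 1.5 × (7.2 + 0.20 × 3.5) = 11.85 v 1.5 × (6.6 + 0.35 × 3.5) = 11.74, nearly equal;
- rates: 11.85/7.2 = 1.65 v 11.74/6.6 = 1.78 per week, a spurious 8% excess.

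With doubling instead, totals are 11.3 v 10.8 and rates 1.57 v 1.64. Each is off, in opposite directions.

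**The case against.** On time at risk, the article never says that totals must be unscaled. Both named tests can be run on per-week counts, and a full analysis plan might do so. Table 1 excludes end-of-life patients and requires KPS ≥ 50, which should limit early loss. Without a difference in loss between arms there is no bias, and a difference could go either way. Total use over eight weeks is also a legitimate quantity for a cost question. All of this stands, and it makes this half the smaller one. What remains is that section 2.10 sends numbers without a denominator to the tests, while another outcome in the same section is given per week.

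On calls, no passage says that the physician responds to a reading by phoning. Section 2.5 speaks of intervention in the home setting, and resulting visits are counted in both arms. The size of any shift is unknown. That also stands, but the definition by calls received appears in both 2.6 and 2.10, so it is fixed rather than left open.

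A reader might infer that contacts about the device or router also go uncounted, so that the call outcome systematically favours the device. The text does not support this. A patient who phones the doctor or nurse about the device makes a call received, and that counts against the device. A reader might also want the totals replaced by a negative binomial model with hospital days removed from the offset. That would condition on an outcome arising after randomisation, which is itself one of the listed outcomes.

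**Conclusion.** The point holds in two parts of unequal weight.

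- **Calls.** The definition omits outgoing calls, which daily review can prompt in one arm only. Any shift in direction appears one for one as fewer calls. The mechanism follows from the text, its size is unknown, and it does not touch visits, emergency attendances or hospital use.
- **Observation time.** Under constant weekly use, a 15-point difference in early loss moves totals by about 8% and a 30-point difference by about 16%, with Mann–Whitney rejection at about 6% and 10% instead of 5%. With equal loss there is no bias.

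It would be tempting to conclude that early death makes the device look cheaper. The article gives no reason to expect more loss in that arm, and if use rises before death the direction is uncertain and per-week rates can mislead as well. Totals and rates are therefore both needed.

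These are secondary outcomes of a 50-patient pilot that section 3 itself treats as indirect evidence on cost. The acceptability and feasibility outcome is unaffected.

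**What to change.** 1. In 2.6 and 2.10, redefine the call outcome as all calls between the care team and the patient or caregiver, in both directions. Log direction and reason in the electronic record described in 2.7, with telemonitoring-triggered and technical contacts identified separately.
2. Report deaths, withdrawals and observed time by arm.
3. Show service use per patient-week under observation, as simple rates or from a count model with log observed time as offset, alongside the eight-week totals. Where the two disagree, say so and interpret them together with the deaths.

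The cost is one extra field for doctors and nurses to complete and a little more analysis. The article says recruitment is under way, so the call field should be added promptly. The direction of calls already made may not be recoverable.

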### 2.4. Recruitment and Randomization

The investigator will be the ANT physician in charge with the home care of the patient. During the first visit, after verifying the inclusion and exclusion criteria, the investigator (ANT physician) will explain the study to the patient and caregiver and propose their participation. If they consent, after collecting informed consent for participation and personal data management, the physician will contact the Research Department of the ANT Foundation to include the dyad (patient and caregiver) in the study.

Participants will be randomly assigned by the Research Department staff to the ButterfLife group (25 patients) or the Control group (25 patients) by randomization using an Excel-generated random number set. Investigators that will run the statistical analysis will be blinded to the randomization procedure.

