Patients in the control group will receive standard home care: visits will be planned according to the patient’s needs. In case of an unstable clinical condition, worsening of symptoms, and alteration of vital parameters, the patient can contact the physician or the nurse by phone, who will decide how to intervene.

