### 2.7. Other Assessments

All the clinical and demographic data of patients, as well as the health care services provided by ANT physicians and nurses, will be collected on an electronic record form exploiting Cloud technology created by Vitaever SaaS (Nethical S.r.l., Bologna, Italy) (https://www.vitaever.com/) (accessed on 15 December 2022).

Data related to patients entering the study will be extracted by the Vitaever database in Excel format. The following data will be used in the study:Demographic data (sex, age).Primary site of disease (recorded according the International Classification of Diseases (9th revision) [34] and then classified as gastrointestinal, respiratory tract, genitourinary, breast, nervous system, haematological, and other), time since diagnosis, and presence of metastases. Disease stage (radically operated cancer (adjuvant therapy—supportive therapy); advanced cancer (early palliative care—supportive therapy); locally advanced cancer (adjuvant therapy); advanced cancer (palliative care only).KPS.Edmonton Symptom Assessment Scale (ESAS) [35].Cancer therapy (chemotherapy, hormone therapy, radiotherapy, immunotherapy) and pain therapy.

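### Service use and FAMCARE-2, which have no Day 1 value, are compared without adjusting for entry KPS; the test is valid but gives up precision and leaves the one realised comparison open to chance imbalance

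*Protocol article*

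**What the plan says.** - **Between-arm comparison (section 2.10).** The list of outcomes includes "number of scheduled visits, unscheduled visits, on-call visits, phone calls received by the doctor and nurse, number of visits to the emergency room", followed by hospital admissions and hospitalization; caregiver satisfaction is also in it. After a Shapiro–Wilk check, each is analysed with Student's t-test "or non-parametric tests (Mann–Whitney test").
- **Use of Day 1 (section 2.10 and Table 2).** Trends "over time (day 1, day 28 and day 56) will be analyzed using a general linear model for repeated measures", but only for quality of life, psychological state and caregiver burden. Table 2 lists FAMCARE-2 at Day 56 only and contains no service-use count. Section 2.4 places recruitment at the first visit, so there is little or no earlier use of this programme to serve as a baseline.
- **Entry data (section 2.7 and Table 1).** "Data related to patients entering the study will be extracted by the Vitaever database in Excel format". The extract includes KPS, disease stage and the "Edmonton Symptom Assessment Scale (ESAS"). KPS of at least 50 is an inclusion criterion, so it is known before randomisation. The article does not date the ESAS or stage values.
- **Role of those data (section 2.10).** The descriptive analysis covers "age, sex, KPS, diagnosis, time since diagnosis, presence of metastases, symptoms, current therapies, and stage of the disease". No other use is stated.
- **Randomisation (section 2.4).** Patients are allocated "by randomization using an Excel-generated random number set". No stratification factor is named.
- **Care (section 2.5).** In the control arm "visits will be planned according to the" patient's needs, and worsening symptoms lead to phone contact.

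**The concern.** Quality of life, psychological state and caregiver burden have a Day 1 value and a model that uses it. Service use and FAMCARE-2 have neither, so the only baseline information available for them is a prognostic variable measured at entry. KPS is such a variable, and the analysis leaves it out. Because the named tests cannot take a covariate, this is a stated choice and not a detail left open.

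If visits and calls follow need, an arm that by chance enters with lower KPS will tend to use more of both. The unadjusted difference then mixes that imbalance with any effect of telemonitoring. Only one randomisation will be realised, and an adjustment chosen after seeing the baseline table would be open to challenge. Section 3 intends to read service use as an indirect measure of impact on costs and resources, so these comparisons will be interpreted.

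**Working it through.** **The plan's own figure.** Section 2.9 gives power 0.86 for a Mann–Whitney test with 25 per arm, effect size 0.8 and α = 0.05. A noncentral t calculation with effective n = 25 × 3/π gives 0.859 one-sided and 0.772 two-sided. The figure therefore reproduces with a one-sided α. The present point does not depend on it.

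**Inputs.** 25 per arm (sections 2.4 and 2.9). Correlation r between entry KPS and the outcome: not given, assumed 0.3 to 0.5. Calculations are two-sided and on the normal scale unless stated.

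**1. Size of chance imbalance.** The SD of the difference in mean KPS, in SD units, is √(2/25) = 0.283.
- 95% range: ±1.96 × 0.283 = ±0.55.
- P(|difference| > 0.3) = 2 × [1 − Φ(0.3/0.283)] = 0.289.
- P(|difference| > 0.5) = 2 × [1 − Φ(0.5/0.283)] = 0.077.

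**2. Effect on the estimate.** An imbalance of 0.5 SD moves the unadjusted difference by r × 0.5, that is 0.15 SD (r = 0.3) to 0.25 SD (r = 0.5). Against the effect size of 0.8 in section 2.9 this is 0.15/0.8 = 19% to 0.25/0.8 = 31%.

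**3. Error rate.** Over all randomisations, 60,000 simulated null trials per value of r gave 0.050 for the unadjusted t-test at both r = 0.3 and r = 0.5. Given a particular imbalance, the rejection rate follows approximately from a statistic with mean r × imbalance/0.283 and SD √(1 − r²), set against the t critical value on 48 degrees of freedom:

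| Imbalance | r = 0.3 | r = 0.5 |
|---|---|---|
| 0 | 3.5% | 2.0% |
| 0.3 SD | 4.5% | 4.5% |
| 0.5 SD | 6.4% | 9.7% |

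Allowing for the estimated SD raises these slightly: at 0.5 SD, simulation gave 7.0% and 10.6%, and at 0.3 SD the rate is close to 5%. Small imbalances are conservative and large ones are not, and they average to 5%.

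**4. Precision gained by adjusting.** Equivalent n per arm = 25/(1 − r²):
- r = 0.3: 25/0.91 = 27.5.
- r = 0.5: 25/0.75 = 33.3.

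The simulated SD of the estimate fell from 0.2821 to 0.2724 (r = 0.3) and from 0.2828 to 0.2476 (r = 0.5). That gives 25 × (0.2821/0.2724)² = 26.8 and 25 × (0.2828/0.2476)² = 32.6, so about 27 to 33 after paying for the estimated slope. Power goes from 0.41 to 0.44–0.52 at d = 0.5, and from 0.79 to 0.83–0.89 at d = 0.8.

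**5. Whether the gain carries over to counts.** Under assumed count distributions, rank-based ANCOVA with one covariate held about 5% error. It raised power from about 0.50 to 0.56 in one setting of frequent counts and from 0.43 to 0.53 in another. A repeat with mean count 6 and dispersion 0.5 showed the same pattern. For rare counts (mean 0.5, dispersion 2) there was no useful gain.

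**The case against.** The strongest reply is that nothing here is an error. A randomised comparison needs no adjustment to be valid, and step 3 confirms 5% overall. This stands. A reader might infer that the planned tests have an inflated false-positive rate; the documents and the arithmetic do not support that. The 9.7% applies only given a 0.5 SD imbalance at the top of the assumed correlation range, and about 8% of trials exceed that imbalance.

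The correlation is also unsupported by any figure. Section 2.5 speaks of need, not of KPS, and eligibility cuts KPS off at 50 and excludes end-of-life patients, which may weaken the link. At r = 0.3 the gain is small. For FAMCARE-2 the article offers no direct link to KPS at all. These points stand and limit the claim to a range.

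A reader might also infer that ESAS and stage are entry values, or that randomisation is shown to be unstratified. Neither is established: section 2.7 gives no dates, and a condensed article that names no stratification factor does not prove there was none.

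Finally, the obvious remedy can do harm. In simulation with 25 per arm, a Wald test from a negative binomial model with one covariate rejected a true null 6.6% of the time for both frequent and rare counts, and 33 of 1,500 fits failed for the rare one. This stands, and it shapes the fix.

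What the objection does not remove is that the article fixes tests that cannot use a covariate already in hand, for the outcomes that have no other baseline.

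**Conclusion.** The point holds as a matter of precision and of protection for the single realised comparison. It is not a point about validity. For visits and calls, adjusting for entry KPS would be worth about 2 to 8 extra patients per arm (27 to 33 instead of 25) if r lies between 0.3 and 0.5. It would also remove a chance shift of 0.15 to 0.25 SD in the roughly 8% of trials where the imbalance reaches 0.5 SD or more. For emergency room visits and admissions, if events are few, the gain is negligible.

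The conclusion rests on the assumed correlation and on normal-scale figures carried over to counts. Its weight is moderate: these are secondary outcomes of a pilot, and the primary outcome of acceptability and feasibility is untouched.

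**What to change.** In section 2.10, before the blinded data are released:

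- For visits, calls and FAMCARE-2, prespecify a between-arm comparison adjusted for entry KPS as one continuous covariate, by a method that holds its error at n = 50. Rank-based ANCOVA is one option. For the counts, another is a count model with log time under observation as offset and permutation or small-sample-corrected inference; it also accommodates unequal follow-up, which matters because section 2.10 expects drop-out.
- Keep the planned t or Mann–Whitney test for these outcomes as a sensitivity analysis.
- Keep the unadjusted test as the main analysis for emergency room visits and admissions if events are few.
- Add ESAS as a second covariate only if its value is confirmed to date from before randomisation.

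KPS is already in the extract, so no new data, visits or patients are needed. The cost is slightly more analysis work and one degree of freedom, with little or no gain if KPS proves weakly prognostic.

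### For zero-heavy hospital and emergency outcomes, the planned rule leads to a rank test that says little about days used, while section 3 reads these outcomes as a measure of resources

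*Protocol article*

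**What the plan says.** Section 2.10 sets one rule for all between-group comparisons: "after analyzing the normality of the variables (Shapiro–Wilk test), the differences between the two groups for secondary outcomes" are tested with Student's t-test "or non-parametric tests (Mann–Whitney test"). The rule covers the questionnaire scores, the "number of scheduled visits, unscheduled visits, on-call visits, phone calls received by the doctor and nurse", and the emergency and hospital outcomes: the "number of visits to the emergency room, number of hospital admissions and hospitalization) will be analyzed with parametric" or non-parametric tests. No comparison of mean amounts is named for the non-normal branch.

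Section 2.6 gives the unit of the hospital outcome: "Hospitalization days will be assessed". Section 2.5 fixes the observation window: "The study will last eight weeks for each patient". Section 3 states what visits, calls, admissions and hospitalization days are for: they "will return an indirect measure of the impact of this telemonitoring intervention in terms of costs and suitability of resources".

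**The concern.** Resources used are an amount: the arithmetic mean per patient times the number of patients. Mann–Whitney asks something else, namely whether a patient in one arm tends to rank above a patient in the other. When most patients have zero hospital days, most pairs are ties, and nearly all the remaining information is whether a patient was admitted at all. How long the admitted patients stayed hardly enters.

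Shorter stays among about the same number of admitted patients would be a real saving, yet the planned test could report no difference. The resource statement would then rest on a test of a different quantity. This holds even if all 50 patients complete the eight weeks.

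**Working it through.** **Inputs.** From the document: 25 patients per arm (2.9), eight weeks (2.5), the test rule (2.10), days as the unit (2.6). The document gives no admission rates or lengths of stay, so every rate below is an assumption for illustration.

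**The plan's own figure.** The power of 0.86 in 2.9 (Mann–Whitney, effect size 0.8, α = 0.05) reproduces as 0.859 for a one-sided test with a normal parent, and as 0.772 for a two-sided test. It assumes normal-shaped data, so it does not bear on zero-heavy outcomes.

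**Which branch is taken.** In simulated zero-heavy hospital days and emergency visits (mean 0.3), Shapiro–Wilk rejected in essentially every run. For frequent counts the branch is open. With Poisson counts, normality was rejected in at least one arm in 50% of runs at a mean of 4 and in 13% at a mean of 24. With overdispersed counts the figure was 90% to 99.8%.

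**Case 1: same share admitted, shorter stays.**
- Take 7 of 25 admitted in each arm. Stays in ButterfLife are 1, 2, 2, 3, 3, 4, 4 (19 days). Stays in Control are 7, 10, 12, 14, 16, 20, 25 (104 days).
- Means are 19/25 = 0.76 and 104/25 = 4.16, a difference of −3.40 days per patient.
- U for ButterfLife = 7 × 18 (admitted v not admitted) + ½ × 18 × 18 (ties at zero) = 126 + 162 = 288. The null value is 625/2 = 312.5. The tie-corrected p is 0.56.
- Every ButterfLife stay is already shorter than every Control stay, so U cannot move further. With k admitted in each arm, the largest possible departure from the null is k²/2 (here 24.5). With complete separation, p is 0.084 at k = 13 and 0.048 at k = 14. Below 14 of 25 admitted in each arm, no shortening of stays alone can reach two-sided 0.05.
- Simulation (24% admitted in both arms, mean stay 6 v 12 days, rounded gamma stays of shape 2): Mann–Whitney rejects in 5–6% of trials, a permutation test of means in 11%.

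**Case 2: more admitted, shorter stays.**
- ButterfLife 10 × 3 = 30 days, Control 5 × 12 = 60 days. Days are halved.
- U for ButterfLife = 10 × 20 + ½ × 15 × 20 = 200 + 150 = 350, and 350/625 = 0.56, so the ranks point against ButterfLife (p = 0.37).
- Simulation (40% × 3 days v 20% × 12 days): rank and mean directions are opposed in about two thirds of trials. Mann–Whitney is significant against ButterfLife in 17–19%, a permutation test of means in 1–2%.

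**Case 3: fewer admitted, stays the same or shorter.** Same simulation model, ButterfLife v Control:

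| Scenario | Mann–Whitney rejects | Permutation test rejects | Directions opposed |
|---|---|---|---|
| 10% × 8 v 30% × 8 days | 42–43% | 31–33% | about 5% |
| 10% × 6 v 30% × 10 days | 45–49% | 47–48% | 1–2% |
| 20% × 8 v 40% × 10 days | 36–37% | 34% | 4–5% |

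No run gave a significant rank result in the wrong direction.

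**Precision of the mean difference.** In Case 2 it is 1.2 − 2.4 = −1.2 days. The sample variances are 2.25 and 24, so SE = √(2.25/25 + 24/25) = √1.05 = 1.02. An approximate 95% interval is −1.2 ± 1.96 × 1.02, or −3.2 to 0.8 days.

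**The case against.** A reader might infer that the planned test will contradict the resource impact. The documents do not support that. Contradiction needs the share admitted and the length of stay to move in opposite directions. The Introduction describes telemonitoring as a way to reduce emergency and hospital admissions, and 2.5 expects early detection to lead to intervention at home. If that happens, Case 3 applies: ranks and means largely agree, and Mann–Whitney can be the more powerful test. This stands, and it is why dropping Mann–Whitney outright is not warranted.

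A reader might also infer that every service-use outcome ends in a rank test. That is too broad, because visits and calls that are frequent and not overdispersed may well reach the t-test.

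Further, these are secondary outcomes of a pilot, section 3 claims only an indirect measure, admissions are tested separately from hospitalization, and a condensed article may leave summary statistics to a fuller document. A comparison of means also gains little power (11% against 5–6% in Case 1). All this limits the weight of the point. What it does not answer is that 2.10 names the test, section 3 names the use, and in Case 1 that test cannot see the change in days. Testing admissions separately does not help there, since the share admitted is equal.

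**Conclusion.** The point holds in a limited form. For emergency visits, admissions and above all hospitalization days, the rule in 2.10 will almost always select Mann–Whitney, which says little about days used. A shortening of stays without fewer admissions can be missed (19 v 104 days, p = 0.56). A reversal is possible but less plausible given what the protocol expects. If share and stay move the same way, the planned test serves adequately.

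The sizes rest on assumed admission shares of 10–40% and mean stays of 3–12 days. The limit of 14 admitted per arm depends only on 25 per arm, equal numbers admitted and the usual large-sample p-value. The primary acceptability outcome is not touched. This is a cheap improvement to a secondary analysis.

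**What to change.** In 2.10, for emergency visits, hospital admissions and hospitalization days, report the difference between arms in arithmetic mean per patient with a bootstrap 95% interval, whatever Shapiro–Wilk shows. A permutation test of means is optional. Keep Mann–Whitney as a supplementary comparison. In section 3, base the resource statement for these outcomes on the mean difference and its interval.

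The change is one of wording and needs no new data. With 25 per arm the interval will be wide, and the text should say so.
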